**Intervention**

The intervention was developed based on the principle of cued actions of the Health Belief Model (Strecher and Rosenstock. 1997). This model states that external cues, such as reminders and prompts, may increase adherence behaviours.

Usual care arm

Participants randomised to the usual care arm will receive standard care for their HF as determined by their treating physicians, including prescriptions to treat CHF and advice, as well as lifestyle advice. The participants in this group will have no access to a smartphone medication reminder application.

Intervention arm

Participants allocated to the intervention arm will have access to the NPS MedicineWise application (MedicineWise app) in addition to standard care (as described above). Once consented, each participant in the intervention arm will be given training by a member of the research team. This training will include how to download the MedicineWise app from the participant’s smartphone application store, navigate the features within the MedicineWise app, how to enter all of their current medications (both CHF related and non-related) into the app (including medication name, strength, dosage form, dose and frequency of administration), how to edit or delete a medication if there are instructed changes from their treating physician, how to set up in-app reminders, how to acknowledge and register a taken dose and troubleshooting and technical support information. The researcher will also provide practical tips to ensure participants can get the best experience from their interactions with the app. instruct participants in the intervention arm how to edit or delete a medication if the medication, dose or timing is either changed or suspended by their treating physician. At the end of the training, participants will be asked to demonstrate to the researcher team member that they can perform these functions on the app comfortably and that they know where and how to seek help should any problems occur.

Tier 1 intervention: in-app medicine dose reminders from the MedicineWise app

Once downloaded and all medication related information has been uploaded onto the application, participants will receive in-app reminders (in the form of notifications and audible alarms, if they choose) when each medicine dose is due to remind them to take their dose. Participants have the option to dismiss or “snooze” the reminder. Dismissing a reminder means that the participant will not receive that specific dose reminder again. “Snoozing” a reminder means the reminder would then be repeated at default 30-minute intervals (the default will be adjusted according to the participant’s preference to truly reflect real-life use of this snooze function). Participants can acknowledge that they have taken their medicine doses in the app by tapping on a “taken” button that is associated with the dose. Information of either the dose being recorded as taken or missed (i.e. not marked as “taken”) will be registered by the MedicineWise app and will be extracted daily at NPS MedicineWise headquarters. A NPS MedicineWise research team member will determine from the extracted data the doses that were missed during the 24 hours prior, according to the criteria set for critical or non-critical medications (see Tier 2 intervention).

Tier 2 intervention: personalised ‘push’ notification messages from the MedicineWise app

Medications have been categorised as critical or non-critical to the management of heart failure (Table 1). If a participant has either missed a dose of a critical medication for 24 hours or a non-critical medication for 3 days, they will receive a personalised ‘push’ notification from the MedicineWise app containing one or more of the following messages: reminding them to take their doses; reminding them to interact with their app; emphasizing the importance of adhering with their medication regimen; how to seek help if they are having difficulty with their medication and/or operating the MedicineWise app.

In the same way as for Tier 1 escalation, a NPS MedicineWise research team member will examine the extracted dosage taken data during the 24 hours prior and escalate participants to the Tier 3 program as required.

Tier 3 intervention: phone call intervention delivered by Medicines Line pharmacists (NPS MedicineWise)

Participants who do not respond to MedicineWise app notifications (Tier 1 intervention) and ‘push’ notification messages (Tier 2 intervention) will be contacted by a NPS MedicineWise’s Medicines Line pharmacist by telephone to discuss their medicines and medication adherence. A NPS MedicineWise research team member will provide the Medicines Line pharmacist with the participant’s details and records in a secure file in a shared drive with password access. Only the NPS MedicineWise research team members and Medicines Line team will have access to this file.

The Medicines Line pharmacist will contact the participant by telephone, as soon as possible (ideally within one working day of the participants’ escalation into the Tier 3 intervention) and record details of the call in MiDatabank® software. Keyword ‘heart failure trial’ can be used to identify calls when retrieving data. Data can be extracted from the Midatabank software to assist with analysis. Five attempts at different times of the day and different days of the week will occur. Details of attempt time and date will be recorded.

Once telephone contact is made, the following details will be recorded in MiDatabank:

- Particpant name, date of birth, postcode, gender, ethnicity, phone number, ‘heart failure trial’ keyword.
- Consent documented to advise UniSA Research Assistant that call has occurred.
- Current medications: medicine name, brand, strength, dosage.
- Details of conversation with patient.
- Details on adherence, including possible reasons for non-adherence eg.side effects, concerns with drug interaction or other reasons – keywords to be documented in MiDatabank
- Success or difficulties with using the MedicineWise application.
- Details of medicine information resources accessed.
- Evidence-based medicine information can be provided using standard resources, including but not limited to:
- Therapeutic Goods Administration Product Information and Consumer Medicine Information
- MIMs
- Australian Medicines Handbook
- Stockleys Drug Interactions
- Details of discussion with patient and information provided, including discussion on importance of heart failure medicines and how to improve adherence. Risk factors for reducing complications of heart failure can also be discussed and documented.
- Patients can be referred to their doctor, specialist or community pharmacist, if clinically indicated.

A participant can be contacted up to a maximum of 3 times by a Medicines Line pharmacist during the trial to discuss medication adherence. Each call will be documented in MiDatabank. Details (including the patient’s name, date of birth, MiDatabank keywords, call category) for each call will be forwarded via secure digital pigeon, with password access, to the research team member at the University of South Australia to inform of the intervention.

Tier 3A intervention: personalised ‘push’ notification messages from the MedicineWise app during weekends

The Medicines Line is an office hour service which will be operative Mondays to Fridays 9 am to 5 pm AEST (excluding NSW public holidays). This is a ‘real world’ intervention. Out of these hours, participants will receive a further personalised ‘push’ notification which will be followed up on Monday morning. If participants are concerned about their medications during the weekend, they will be advised to follow their standard medical care plan and contact their own doctor, pharmacist or emergency services if applicable.

Other features of the MedicineWise app

Other features within the MedicineWise app, includes the ability to have multiple profiles (carer mode) and the ability to record health conditions, allergies, test results and other health information. Recent enhancements have also enabled the app to deliver featured health- and medicine-related content to users based on their medicines and/or health conditions. Participants in the intervention arm will be able to use any of these features within the MedicineWise app; however such additional data collected by the app will not be used for the purposes of the current study.

**Outcome measures**

Outcome measures will be collected at 3, 6 and 9 months following the baseline data collection at recruitment.

Primary outcome

The primary outcome is the comparison of medication adherence between the two arms. Medication adherence will be measured by self-reported medication adherence tool Self-Efficacy for Appropriate Medication Use Scale (SEAMS) (Risser et al., 2007). This has been validated previously in other cardiac conditions such as coronary heart disease (Risser et al., 2007). This self-reported data will also be verified by the data collected from the intervention arm participants whose adherence rate has been captured by the data collected by the NPS MedicineWise application.

Secondary outcomes

i. composite outcome of death or hospital admission related to HF or not related to HF. All instances of hospitalization and death will be recorded and classification as to whether it was HF related or not will be done by experienced cardiologists

ii. health resource utilization (ie. Primary and secondary care contacts, social care contacts and relevant medication use)

iii. health related quality of life, assessed by EQ-5D-5L

iv. self-reported medication adherence

v. assessment of exercise tolerance (6 min walk test)

vi. psychological wellbeing (Depression anxiety and stress scales)

vii. self-care of HF index questionnaire

viii. medication knowledge

ix. acceptability, utility and engagement with the NPS MedicineWise application (Satisfaction survey)

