**[name] (Noarlunga GP Plus)**

**[name] (ICCNet)**

**Associate Investigators: [name]**

**[name]**

**[name]**

**[name]**

**[name] (Study RA; Masters student)**

**Introduction**:

Heart failure (HF) is a complex clinical syndrome characterized by the reduced ability of the heart to pump and/or fill with blood, causing a significant burden for patients and healthcare systems in developed countries. HF is increasing in prevalence affecting at least 26 million people worldwide (Savarese & Lund, 2017). HF accounts for approximately 1-3% of overall healthcare spending, mainly due to repeated hospital admissions and prolonged inpatient length of stay (Sahle et al., 2016). However, the return of investment in healthcare spending in HF is very poor as studies suggest that approximately 50–75 % of patients with HF die within five years of diagnosis and this expenditure has been estimated to increase dramatically with an ageing population (Sahle et al., 2016).

Despite the significant advances in therapies and prevention, non-adherence with medication in HF patients is associated with excess mortality and morbidity. Medication adherence is defined as the extent to which a patient takes medications as prescribed by their healthcare providers (Chowdhury et al., 2013). While the World Health Organization describes poor adherence as ‘a worldwide problem of striking magnitude,’ it is a problem that should be viewed as ‘diagnosable and treatable’ (Marcum et al., 2013; WHO, 2003).

A systematic review estimated adherence to medications for HF to be 48.4% (95% CI 9.0% to 89.2%) (Bowry et al., 2011). Suboptimal adherence is recognized as a global challenge to health systems, due to its strong association with an increased risk for poor health, adverse outcomes and mortality (Forsytha et al., 2019; Hines et al., 2018). For example, Chowdhury et al. estimate that of all adverse medication reaction-related hospital admissions in the USA, 33–69% are due to poor medication adherence with an estimated cost of $100 billion (Chowdhury et al., 2013).

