While Bowry et al. (2011) report that adherence does not significantly change according to gender, age or the complexity of medication regimens, factors which significantly influence adherence levels are low social status, low health literacy, existence of co-morbid conditions, and polypharmacy (Bowry et al., 2011). Other common predictors of poor adherence include negative perceptions about medication, side effects and high medication costs (Bowry et al., 2011). Furthermore, self-efficacy for appropriately taking HF medications may be predictive for physical health status where individuals with higher self-efficacy report better physical health status, including symptom control, and quality of life. Clinically, higher self-efficacy has been found to improve cardiac function, which may explain improvements in physical health status as symptom burden is less. Consequently, supporting people’s self-efficacy and confidence in their selfcare activities will impact their medication adherence, condition control and health status (Como 2018).

The use of the internet and smartphones to deliver health care is growing rapidly (Becker et al., 2013). Mobile health (mHealth) interventions, such as smartphone applications (apps), have been advocated as promising strategies to assist in the self-management of hypertension and other chronic conditions. The number of smartphones worldwide is predicted to reach 5.8 billion by 2020 and there are 6 million multimedia applications (apps), of which 318,000 are mHealth apps, available for download in the app stores (Byambarsuren et al., 2018). With the global prevalence of mobile technology, accessing health-related applications via mobile phone seems a logical step in the patients’ management of their own medical conditions. While there is still a threefold ‘‘digital divide’’ between age groups, sexes and according to education levels, it seems likely that mHealth apps will increasingly play a role for elderly and chronically ill users (Becker et al., 2013). However, guidance and coaching by the healthcare provider will be necessary and not overloading an application with functionality is essential when developing for elderly users with chronic conditions (Becker et al., 2013).

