**Hypothesis**:

The primary hypothesis is that reminders via a smartphone application with a personalized and progressive monitoring system plus usual care (as received by participants in the intervention arm) compared with usual care alone (as received by participants in the control arm) will be associated with higher medication adherence, at 9 months’ follow up.

The secondary aims of this trial includes:

1. to determine whether a smartphone application reminder with interactive and personalised monitoring is cost effective, as determined by lower health services utilization, at 9 months’ follow up;

2. to determine the impact of the smartphone application on signs and symptoms of heart failure and quality of life at 6 and 9 months;

3. to determine whether the intervention is associated with higher medication and heart failure knowledge;

4. to determine the feasibility, acceptability and engagement with the application as determined by the

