**Sample size**

Sample size calculations are focused on two different measures and were also done assuming equal numbers of participants in each group. The first measure takes into account an absolute increase in mean adherence of 15 % (Hulley et al., 2013). In this measure, at two tailed 0.05 significance level with a power of 80 % and standard deviation of 35 (Goldstein et al 2014), the number of participants required in each group is 86. In the second measure, the analysis is by comparing proportions of adherence (Hulley et al., 2013). Previous studies have estimated the adherence to cardiovascular drugs to be up to 60 % (Chowdhury et al., 2013; Bowry et al., 2010). In this measure, a total sample size of 182 participants is needed to provide 80 % power to detect an increase in the proportion of adherent participants from 60 % to 80 %, with a two tailed 0.05 significance level. Therefore, taking the larger of the two sample sizes (91 participants in each arm), and allowing for a 20 % loss to follow up, a total of 220 participants will be recruited in this study with each arm consisting of 110 participants.

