**Trial data collection**

Trial data will be collected at 4 time points (at baseline, 3, 6 and 9 months). Data will be collected at face-to-face during home visits, phone calls or via skype interviews (mainly for rural participants). To encourage participant retention and completeness of data, participants will receive a honourarium of AUD$30 in total at completion of the study.

At the point of recruitment into the trial, baseline data will be collected after written informed has been obtained by a member of the research team. The following information will be collected:

Sociodemographic information: Date of birth, gender, ethnicity, height, weight, education status, marital status, employment status, smoking status and health literacy

Medical history: comorbidities, NYHA class, standardised mini-mental state exam score, depression score, all prescribed and non-prescribed medication history

Laboratory test results: full blood counts, full electrolytes (sodium, potassium, urea, creatinine +/- magnesium), Hb, iron studies, NT pro BNP, liver function tests.

Functional assessment: QoL questionnaire using the Short Form 36 Health Survey version 2 (SF-36v2) (Ware JE; RAND Corporation 2015), Depression Anxiety and Stress Scales (DASS), Self-Care of Heart Failure Index (SCHFI) (Riegel et al., 2009), EQ-5D-5L questionnaire (Herdman et al., 2011) and drug adherence questionnaire, healthcare utilization (linkage data from Australian Pharmaceutical benefits Scheme and Medicare Benefits Schedule).

At the 3, 6 and 9 month follow ups, a member of the research team will record details of any changes to the participants’ medication or implantable cardiac devices, details of any hospitalisations or healthcare resource utilization since the last follow up. At each follow up interview, participants in the control arm will be asked whether they have used any drug administration aids or medication reminder app or other forms of electronic reminder systems for daily administration of medications. At the end of the study, intervention arm participants will complete a satisfaction survey to assess the acceptability, utility and engagement with the NPS MedicineWise application. Also, data about prescription refill rates and healthcare utilization will be gathered for all participants through data linkage with the Australian Pharmaceutical benefits Scheme and Medicare Benefits Schedule.

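### The primary outcome is a self-efficacy scale, but the hypothesis and both sample-size calculations concern adherence, so the stated 80% power is unsupported for the named measure

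*Protocol*

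**What the plan says.** The Introduction defines the target as a behaviour: "Medication adherence is defined as the extent to which a patient takes medications as prescribed by their healthcare providers". It then places self-efficacy upstream, saying that supporting "self-efficacy and confidence in their selfcare activities will impact their medication adherence, condition control and health status". The Hypothesis section expects that the intervention "will be associated with higher medication adherence, at 9 months".

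Under Outcome measures, the primary outcome is a between-arm comparison of adherence, and the instrument is fixed: "Medication adherence will be measured by self-reported medication adherence tool Self-Efficacy for Appropriate Medication Use Scale (SEAMS"). The same paragraph adds: "This self-reported data will also be verified by the data collected from the intervention arm participants", using the adherence rate that the app captures. Self-reported medication adherence appears again as secondary outcome iv, with no instrument named.

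The Sample size section uses two adherence quantities. One is a difference in means: "The first measure takes into account an absolute increase in mean adherence of 15" %, "at two tailed 0.05 significance level with a power of 80 % and standard deviation of 35", giving 86 per group. The other is a rise in the proportion adherent from 60% to 80%, giving 182 in total. The larger governs and is raised to 220 (110 per arm) for 20% loss. SEAMS is not mentioned there.

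Trial data collection states that "data about prescription refill rates and healthcare utilization will be gathered for all participants through data linkage" with the Pharmaceutical Benefits Scheme (PBS) and Medicare Benefits Schedule.

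**The concern.** The hypothesis, the primary instrument and the sample size should describe the same quantity. Here the first and third describe medicine-taking, and the second measures confidence about medicine-taking. By the Protocol's own account these are different things, one acting on the other.

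Two consequences follow. A positive primary result would show that trained and reminded participants report more confidence, which is weaker than the adherence claim that the Hypothesis and Conclusion sections are built around. A null result would be hard to read, because nobody has stated what SEAMS difference the trial can detect or whether that difference is plausible.

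The stated verification does not close the gap. A log of doses marked as taken is a different quantity from a confidence score, and data from one arm cannot support a comparison between arms.

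**Working it through.** **1. Reproduce the Protocol's figures** (two-sided 0.05, 80% power, 1:1; z-values 1.96 and 0.8416).

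- Means: n per arm = 2 × (1.96 + 0.8416)² × 35² / 15² = 2 × 7.849 × 1225 / 225 = 85.5, so 86. Stated: 86.
- Proportions, 60% against 80%, mean 70%: n = [1.96 × √(2 × 0.7 × 0.3) + 0.8416 × √(0.6 × 0.4 + 0.8 × 0.2)]² / 0.2² = (1.270 + 0.532)² / 0.04 = 81.2, so 82 without continuity correction. With correction: (81.2 / 4) × [1 + √(1 + 4 / (81.2 × 0.2))]² = 90.9, so 91 per arm, 182 in total. Stated: 182.

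Both figures reproduce from their own inputs, so the arithmetic of these two calculations is not in dispute.

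**2. Look for a link from those inputs to SEAMS.** The 15 points and SD 35 are on a percentage-adherence scale; the SD is cited to a feasibility trial of telemedicine reminder systems. The 60% and 80% are proportions of participants classed as adherent. The Protocol gives no SEAMS SD, no target difference in SEAMS points, and no SEAMS score that would class a participant as adherent. Power for SEAMS therefore cannot be computed from the document.

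**3. Show the range instead.** After the planned 20% loss, 110 × 0.8 = 88 per arm remain. With d the difference in SEAMS standard deviations, power ≈ Φ(d × √(88/2) − 1.96) = Φ(6.633d − 1.96). The values of d are assumptions; 0.43 is 15/35, the standardised difference implied by the means calculation.

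| d (assumed) | 6.633d − 1.96 | Power at 88 per arm |
|---|---|---|
| 0.2 | −0.63 | 26% |
| 0.3 | 0.03 | 51% |
| 0.4 | 0.69 | 76% |
| 0.43 (15/35) | 0.88 | 81% |
| 0.5 | 1.36 | 91% |

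The difference that gives 80% power is (1.96 + 0.8416) / 6.633 = 0.42 SD.

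**4. Set the adherence data sources side by side.**

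| Source | Arms | Self-reported? | Assigned use |
|---|---|---|---|
| SEAMS | both | yes | primary outcome |
| Self-reported adherence, instrument unnamed | not restricted to one arm | yes | secondary outcome iv |
| App dose log | intervention only | yes: the participant taps to record a dose and can change its time | check on SEAMS |
| Refill rates by linkage | both | no | no adherence outcome |

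PBS data do have other uses. The economic analysis draws on them, and secondary outcome ii (resource utilization) includes relevant medication use. What is missing is an adherence outcome built on refill.

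**The case against.** SEAMS is a published scale, and the Protocol cites earlier validation in coronary heart disease. That supports using it, but the Protocol does not say that it was validated as a measure of doses taken, and the cited source is not at hand. The Data analysis section plans t-tests for continuous variables, so a SEAMS cut-off is not needed to analyse the score. That stands; the cut-off matters only because the proportions calculation sets the final sample size. Definitions of derived variables may sit in an analysis plan that is not shown, but the choice of primary instrument and the basis of the sample size are fixed in the Protocol.

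A reader might go further in five ways that the document does not support.

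- **That the trial is underpowered.** No SEAMS SD or target difference is given, and a true difference of 0.42 SD or more would give at least 80% power.
- **That the refill data go unused.** PBS data feed resource use and the economic analysis.
- **That checking one arm makes measurement differ between arms.** The primary outcome compares SEAMS between the arms, and nothing says that scores will be corrected from app data. The check is uninformative about the control arm; it does not alter the primary measurement.
- **That the trial can say nothing about adherence.** Secondary outcome iv addresses it, though by self-report and with no instrument named.
- **That refill adherence fits the existing calculation because it can be put on a percentage scale.** Nothing shows that SD 35 was obtained from refill data, so carrying it over would repeat the same fault.

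On reporting bias, controls are blinded to the intervention and analysts are blinded. This helps, but it does not remove the influence of training and reminders on what intervention participants report.

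**Conclusion.** The point holds as a mismatch between construct and measure, with an unsupported power statement. The mismatch rests on the Protocol's own definitions and needs no outside figure. As written, the primary analysis can support a conclusion about medication self-efficacy, not directly about medicines taken as prescribed.

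The size of the power problem is unknown rather than large. The range of 26% to 91% depends on assumed differences of 0.2 to 0.5 SD, a two-sided 0.05 test, a normal approximation and 88 analysed per arm. The 80% claim carries over to SEAMS only if a difference of about 0.42 SD is realistic, and the Protocol offers no argument that it is.

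Whether refill adherence should replace SEAMS as the primary outcome is a judgement for the sponsor. That it should be a named adherence outcome in both arms is the firmer conclusion.

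**What to change.** 1. Name refill-based adherence over the 9 months, in both arms, as a prespecified adherence outcome. Key secondary status is enough; if the sponsor makes it primary, it needs its own justified SD and target difference.
2. Use it, in place of app data, as the check on self-report. Treat app logs as engagement data for the intervention arm.
3. Label SEAMS as medication self-efficacy. If it stays primary, word the hypothesis and conclusion accordingly.
4. Either restate power as about 80% for a standardised SEAMS difference of 0.42 to 0.43 SD and justify that difference, or recalculate with a SEAMS SD and target difference. Restating without a justification would only fit a difference to the existing sample size.

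The cost is mainly wording plus analysis of linkage data already being gathered. There are two real drawbacks. The Ethics and dissemination section requires additional individual consent for linkage, so some refill data will be missing, a loss that the 20% allowance does not evidently cover. And a refill shows that medicine was supplied, not that it was taken, so it too falls short of the Protocol's definition of adherence.

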**Data that is captured by the MedicineWise app**

The dataset for each patient in the intervention arm can be generated on a daily basis and exported in a spreadsheet format and can be used by the project team. The type of raw data that is captured is divided into four categories and described below. Further manipulations of this raw data may be necessary (e.g. to identify the participant and to calculate the number of doses missed) and will be carried out as part of the analysis in this study.

The 4 fields of data are:

1. **User ID** – the data extracted from the app will be a unique key that will then need to be de-identified to reveal the participant’s name, DOB, sex and email address. There will be a map provided at the beginning of the study once the participants have been recruited has downloaded and have registered with the MedicineWise app that will enable this process to occur, and a simple Excel matching function should make things easier
2. **Medicine details** – this will include all the medicines that the participant has on their medicines list in the MedicineWise app that are on the critical and non-critical list, and it would include the name of the medicine, strength and form.
3. **Dosage and frequency**– this will include how the patient has been instructed to take their medicines, as entered in the app. In addition to the dose and frequency, it will also include specific times that doses are due.
4. **Actual time when doses are recorded as taken**– when the doses are recorded as taken, timestamp of when that occurs is recorded by the MedicineWise app. The participant has the ability to change that time if they wish (e.g. if a medicine dose is due at 8am and took their dose at 8.30am but they only marked their dose as being taken at 6pm, the app will record the time taken as 6pm but the patient has the ability to change this back to 8.30am). The difference between the time taken and when the doses were supposed to be due will be calculated and used monitor medication adherence.

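### The app log cannot verify the self-reported primary outcome: it exists in one arm only and records an untapped dose as a missed dose

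*Protocol*

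**What the plan says.** **Primary outcome.** Under Outcome measures, the protocol states: "Medication adherence will be measured by self-reported medication adherence tool Self-Efficacy for Appropriate Medication Use Scale (SEAMS"). It continues: "This self-reported data will also be verified by the data collected from the intervention arm participants whose adherence rate has been captured" by the app.

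**Who has app data.** Under Intervention, the usual care arm is described thus: "The participants in this group will have no access to a smartphone medication reminder application". The section on data captured by the app describes a dataset for intervention participants only.

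**How a dose is recorded.** Under Intervention, Tier 1: "Participants can acknowledge that they have taken their medicine doses in the app by tapping on a" button labelled *taken*. On the alternative: "Information of either the dose being recorded as taken or missed (i.e. not marked as" *taken*) is registered by the app and extracted daily. On the recorded time, the data-capture section says: "The participant has the ability to change that time if they wish". Its example is a dose taken at 8.30am but marked at 6pm. The same section leaves the count of missed doses to later processing of the raw data.

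**Engagement.** The last secondary outcome is "acceptability, utility and engagement with the NPS MedicineWise application (Satisfaction survey"). Trial data collection fixes the timing: "At the end of the study, intervention arm participants will complete a satisfaction survey".

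**A source common to both arms.** Trial data collection also plans prescription refill data for all participants through Pharmaceutical Benefits Scheme (PBS) linkage. Ethics and dissemination makes linkage subject to a separate individual consent. Neither section gives the refill data a role in checking the primary outcome.

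**The concern.** To verify a self-reported primary outcome is to claim that it has been tested against something independent of it and relevant to the comparison being made. The app log falls short on both counts. It depends on the participant's own action, as the questionnaire does. It also exists in one arm, whereas the primary hypothesis concerns a difference between two.

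Two things are at stake. The first is interpretation. Agreement between log and SEAMS would be one participant report matching another, and disagreement could mean missed medicine or merely an untapped button. A trial report that called the primary outcome verified would claim more than the data can give.

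The second is a risk that the text leaves open. Data collectors are not blinded (Design). The role description at the end of the protocol gives one person recruitment, app training, liaison with the app staff and all follow-ups. The protocol does not say what happens when log and questionnaire disagree. If a disagreement ever led to a query, that could happen in one arm only.

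**Working it through.** No figure in the protocol depends on this point, so there is none to reproduce. The check sets the passages side by side, with a short calculation to show what the log can and cannot identify.

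**Step 1. Coverage.** Sample size plans 110 participants per arm. App data can exist for at most 110 of 220 (50%): up to 110 of 110 in the intervention arm and 0 of 110 in the control arm.

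**Step 2. What the comparison needs.** Let e_I and e_C be the mean self-report error in the intervention and control arms. Then:

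observed difference = true difference + (e_I − e_C).

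Even a perfect log would inform e_I only. With no log among controls, e_C is unknown, and so is e_I − e_C. A one-arm check cannot support the between-arm comparison, however good the log is.

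**Step 3. What the log measures within its arm.** Let a be the share of doses truly taken, t the share of taken doses that are tapped, and f the share of untaken doses that are tapped. Under the protocol's recording rule:

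log rate = a × t + (1 − a) × f.

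The protocol gives no values for a, t or f, so those below are assumptions for illustration.

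- a = 0.80, t = 0.90, f = 0: 0.80 × 0.90 = 0.72.
- a = 0.90, t = 0.80, f = 0: 0.90 × 0.80 = 0.72.

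Two people with different adherence give the same log. Now hold a at 0.80 and let t run from 0.60 to 1.00 and f from 0 to 0.10:

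- lowest: 0.80 × 0.60 + 0.20 × 0 = 0.48;
- highest: 0.80 × 1.00 + 0.20 × 0.10 = 0.82.

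Over this assumed range, the same true adherence of 80% appears as anything from 48% to 82%. The log carries information on a, but cannot separate it from t and f.

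**Step 4. Does another passage separate them?** The data-capture section gives no rule that tells an untapped dose from an untaken one. The Intervention section itself allows for the ambiguity: a Tier 2 message may prompt the participant to interact with the app, and the Tier 3 call records difficulties with using it.

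**Step 5. Does the log enter the primary analysis?** Data analysis specifies a between-group, intention-to-treat comparison. It does not mention app data, and no passage says that a SEAMS value will be replaced or adjusted from the log. On the text as it stands, the check does not move the SEAMS estimate.

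**Step 6. Engagement.** The engagement outcome names only a satisfaction survey, given at the end of the study. Data analysis adds a thematic analysis that links observed and self-reported responses, including those at months 3 and 9, to engagement. Neither section defines a quantitative engagement measure from the log, although the log is extracted daily.

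**The case against.** The strongest reply is that the sentence does little harm. SEAMS remains the measure, the arms are compared as randomised, and the method of verification may be set out in a statistical analysis plan that is not at hand, perhaps as a simple within-arm agreement analysis. This stands as far as the estimate is concerned. It does not rescue the word *verified*, because no within-arm analysis can show that self-report error is equal across arms.

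The protocol also has safeguards. Participants are trained to edit or delete changed medicines and must demonstrate that they can use the app. Unmarked doses trigger push messages and then a pharmacist call that records reasons for non-adherence and difficulties with the app. These should reduce false misses and help to explain some of them. However, contacts are capped at three per participant, the calls yield no dose-level rule, and nothing comparable exists for controls.

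Some stronger readings are tempting, and the documents do not support them:

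- A reader might infer that the check biases the treatment effect. No passage says that SEAMS values will be queried or corrected from the log.
- A reader might set a shortfall in the log against the 15-point effect in Sample size. The log does not enter that comparison, and any tapping rate would be assumed.
- A reader might infer that dismissing a reminder makes the dose count as missed. The protocol says only that the reminder is not repeated; the dose can still be marked.
- A reader might take the editable time as proof that the taken status is unreliable. Editing changes the time, not the status. It does mean that the timing measure also rests on the participant's entry.
- A reader might conclude that engagement rests on the survey alone, or that the log measures app use and nothing else. Data analysis also draws on observed responses, and the log reflects both adherence and app use.

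**Conclusion.** The point holds in a limited form. As described, the app log cannot verify the primary outcome. It covers none of the 110 planned controls, it depends on the participant's own tap, and it registers every unmarked dose as missed. It cannot separate app use from adherence, nor show whether self-report error is the same in both arms.

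The size is a matter of interpretation, not of a number: no sample size, power or effect figure changes, and the SEAMS comparison is not shown to be biased by the check. The conclusion follows from the protocol's recording rules and from the absence of an app in the control arm. It does not depend on the illustrative values of a, t and f. It is worth correcting because the remedy uses data already planned.

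**What to change.** 1. Under Outcome measures, delete the verification sentence, or reword it as a descriptive comparison of SEAMS with the app log within the intervention arm. State that no SEAMS value in either arm will be queried or altered using app data.
2. Name the PBS refill data, already to be gathered for all participants, as the supportive adherence check. Apply it identically in both arms, among those who give the linkage consent described under Ethics and dissemination.
3. In the engagement outcome, add measures from data already held: share of scheduled doses acknowledged by month, date of the last dose marked, and number of Tier 2 and Tier 3 escalations. Report them for all participants randomised to the app whose data are available; Study population currently excludes the data of those who withdraw. Keep the survey for acceptability and utility.

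**Cost.** The sponsor gives up the statement that self-report was verified. Refill data measure supply rather than ingestion and cover only those who consent to linkage. The acknowledged-dose share still mixes engagement with adherence and should be labelled as acknowledgement. No new data collection is needed, only changed wording and a little more analysis.
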